### Patient screening

**Figure 1** displays the trial flow. Before enrolling a patient, a comprehensive assessment will be performed to determine whether the patient meets the enrollment criteria. The results of the endoscopy and pathological analysis will be used to determine whether the classification criteria of Siewert II AEG are met. CT, enhanced CT, MRI, PET-CT and endoscopy will be used to identify and judge the tumor infiltration depth and the possibility of distant metastasis. A physical examination and laboratory tests for the patients are also essential screening methods. In addition, the medical history and basic demographics should be included in the complete preoperative work-up.

**Figure 1 f1:**
[figure not shown]
Flow chart.

### Patient inclusion and randomization

After all of the patients have completed the baseline assessment, they will be reviewed on a case-by-case basis according to the trial’s inclusion and exclusion criteria. Subsequently, an opaque envelope will be unsealed by a research assistant who is not involved in the recruitment and review of patients. This envelope contains a random number table for randomly assigning people who meet the trial requirements to either the RTA or TH group. The patients and surgeons cannot be blinded to their assignment, whereas the pathologists will be blinded to the patient’s group assignment.

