### Intervention

An equal number of patients will be randomly assigned to the RTA and TH groups. Details of the surgery are determined by the surgeons at each center as long as the tumor can be resected completely. If the tumor is difficult to be resect under minimally invasive conditions, the surgical strategy will be adjusted at that time.

The TH approach will be performed by distal esophagectomy and mediastinal lymph node dissection *via* the diaphragmatic hiatus under laparoscopy, whereas the RTA approach will be performed under thoracoscopy. The resection margin is a key indicator for evaluating the curative effect of surgery. The 5-year mortality of patients with positive resection margins is significantly higher than that of patients with negative resection margins (21).

According to the NCCN guidelines (6) and the Chinese expert consensus, for Siewert type II AEG with cT1 stage, the upper esophageal resection margin is recommended to be at least 2 cm away from the tumor, while for patients with cT2 stage or above, the upper esophageal resection margin is recommended to be at least 5 cm away from the tumor if the RTA approach is performed and at least 3 cm if the TH approach is performed. For patients in the former staging category, the lower resection margin is recommended to be at least 3 cm, while for patients in the latter staging category, a minimum of 5 cm is required to meet the surgical requirements. Laparoscopic proximal gastrectomy can be performed regardless of the surgical approach if the above criteria for the lower resection margin are met and at least more than half of the residual stomach remains.

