### Data collection and management

The clinical data will be completely, timely, accurately and truthfully recorded in the CRF table by the study coordinator. Any changes that are made will be signed and dated by the person concerned, but these changes will never involve the original data. Since randomization is centralized, each participating center will use thestratified-field block-randomization method (25). The study coordinator randomly assigned study populations meeting inclusion and exclusion criteria to either the RTA group or the TH group based on random numbers drawn from the hidden envelope. And each center will assign another study coordinator to be responsible for the data entry and uploading. The project sponsor or the clinical coordinator on behalf of the sponsor will be in regular contact with the center to provide information and technical support. In this way, the investigators can be supervised to strictly implement the study protocol, and to a certain extent, the accuracy of the clinical information on the CRFs can be verified. Authorized representatives of the project undertaking units, regulatory authorities, and ethics committees have the right to audit and inspect the works of each research center at any time, including original data verification. The purpose of an audit or inspection by the project undertaking unit is a comprehensive and targeted review of all study-related activities and documentation, which can guarantee that these activities are supervised in accordance with the guidelines of the research proposal and other regulatory requirements, and the clinical data are accurately analyzed, recorded and reported.

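### The two descriptions of randomization disagree on who allocates and by what mechanism, so allocation concealment is not secured

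*Protocol article*

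**What the plan says.** Two sections of the protocol article describe how a patient gets an arm.

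- **Patient inclusion and randomization.** After baseline assessment and a case-by-case eligibility check, "an opaque envelope will be unsealed by a research assistant who is not involved in the recruitment and review of patients". On the contents: "This envelope contains a random number table for randomly assigning people who meet the trial requirements to either the RTA or TH group". The same section says that patients and surgeons are unblinded and pathologists are blinded.
- **Data collection and management.** "Since randomization is centralized, each participating center will use" a stratified block method. Then: "The study coordinator randomly assigned study populations meeting inclusion and exclusion criteria to either the RTA group or the TH group", and this is done "based on random numbers drawn from the hidden envelope". The same section has clinical data "recorded in the CRF table by the study coordinator", and gives data entry and uploading to a second coordinator at each center.

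Two other sections bear on the point. Study design states that surgeons, patients and coordinating researchers know the allocation. The inclusion criteria require that the tumor be safely resectable by both approaches, which is a clinical judgement made before allocation.

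**The concern.** Concealment means that nobody who decides on a patient's entry can know or guess that patient's arm beforehand. It matters more here than in a blinded trial. Arms already assigned are known at the site, and entry depends partly on whether a surgeon considers both operations safe. A person who knew the next arm could apply that criterion more strictly or more loosely, or could delay a patient. The arms could then differ in prognosis at entry, and analysis cannot reliably correct for differences in unmeasured factors.

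The article gives one safeguard, an opener from outside recruitment, and then describes allocation again without it. Six centers cannot tell from this text which procedure to follow and may adopt different ones.

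**Working it through.** No figure in the plan has to be reproduced, so the check is a comparison of the text.

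| Element | Patient inclusion and randomization | Data collection and management | Compatible? |
|---|---|---|---|
| Who allocates | Research assistant outside recruitment and review | Study coordinator; independence not stated | No, unless the two titles mean the same person or split the task, which is not said |
| Where | Not stated; an envelope is opened | Called centralized, yet applied by each center from an envelope | Unclear; the link between central and local steps is not described |
| What is in the envelope | A random number table | Random numbers that are drawn | Not as worded; reading a table and drawing numbers are different acts |
| Sequence type | Not stated | Stratified blocks | Yes; a table can carry a block list |
| Timing | After the eligibility review | For patients who meet the criteria | Yes |

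**Step 1: the person.** The first section's protection rests on the opener having no part in recruitment or review. The second names a different role and does not repeat that condition, so the safeguard is unsettled.

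**Step 2: the mechanism.** Central release and opening an envelope at a site are different ways to disclose an assignment. They can be combined if a central office prepares the envelopes, but the article does not say so.

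**Step 3: what unsealing discloses.** A table, by the ordinary meaning of the word, holds several assignments. Opening it after the eligibility review protects the patient then being allocated. It does not protect the next patient, because the table has already been unsealed.

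**Step 4: scale, as illustration only.** The article gives no block size. Suppose 1:1 permuted blocks of a fixed, known size b, with all past assignments known. The expected share of assignments that can be predicted with certainty is 2/(b + 2):

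- b = 2: 2/4 = 50%
- b = 4: 2/6 = 33%
- b = 6: 2/8 = 25%
- b = 8: 2/10 = 20%

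As a check for b = 4, the patterns AABB, ABAB and ABBA leave 2, 1 and 1 forced assignments. The mean is 4/3, and (4/3)/4 = 1/3. For someone who has seen the whole table, the share is 100%. A visible table is therefore a larger breach than the predictability that fixed blocks leave in any open-label trial.

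**The case against.** The strongest reply is that the two sections can be read together. A block list generated centrally, stratified by center and sent to sites in envelopes would satisfy the words centralized, block and envelope. The assistant might unseal while the coordinator records the result. The phrase about a table may be loose wording for one number per envelope. The opener in the first section has no part in recruitment and acts only after eligibility is settled, and the second section does not say that the coordinator recruits. Recording the CRF is not recruiting. Envelope numbering, block size and custody of the list are details that an article may leave to the full protocol.

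Much of this stands. Such a scheme would be coherent, and the absence of those details is not the finding. What remains is that the article names two different allocators and two different acts, and says nothing that joins them. A harmless reading has to be supplied by the reader.

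Three stronger readings are tempting, and the documents support none of them:

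- A reader might infer that recruiters or surgeons will see later allocations. No section says so; literally, only the person who opens the envelope is exposed to them.
- A reader might infer simple randomization, and so a conflict with the statement under Intervention that "An equal number of patients will be randomly assigned to the RTA and TH groups". The article never states simple randomization. It names a block method, which is consistent with equal groups.
- A reader might divide the 212 patients by six centers to count the assignments that one table would reveal. That assumes one table per center and equal recruitment, and the article states neither.

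**Conclusion.** The concern holds as a contradiction in the current text about who allocates and how, with a possible consequence for concealment. If the first section is followed literally, the opener can see later assignments. If the second is followed, the opener's independence is not assured. Either could allow selection bias in an open-label trial with a judgement-based entry criterion.

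The wording should stay at can expose, not does expose. The conclusion assumes that a table means more than one assignment, and that the two role titles refer to different people. The direction and size of any bias cannot be derived from the documents; the percentages above describe predictability under assumed block sizes, not bias. It is still worth settling firmly, because an allocation that was not concealed cannot be repaired afterwards for patients already assigned.

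**What to change.** Put the same procedure in both sections, covering these points:

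1. The list is generated centrally in blocks, stratified by center, and the text says who generates it and who holds it.
2. Each assignment is released only after that patient's consent and eligibility have been logged.
3. Release is by a person with no role in recruitment or eligibility review, under one role title used throughout.
4. Release is either central or through sequentially numbered, sealed, opaque envelopes that hold one allocation each.
5. The references to a random number table and to drawn numbers are deleted.

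Release by web or telephone and randomly varying block sizes would strengthen concealment but are optional; the contradiction can be resolved without them. The cost is minor rewording, plus preparing the envelopes or keeping an allocation log. The sample size and the analysis do not change.

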### Patient follow-up

According to the schedule (**Table 1**), the patients will be followed for the first time one month after surgery and then every three months for three years. An additional follow-up survey of the indicators will be conducted semiannually for the next two years. All patients will be required to be followed for at least five years. Each follow-up will include a physical examination, a routine blood examination and a serum tumor marker examination every three or six months. Enhanced thoracic and abdominal CT will be performed every six months, and gastroscopy will be performed annually. If a tumor recurrence or metastasis is suspected, additional tests will be performed and recorded on the CRF table. Trial-related complications will be assessed based on the Clavien−Dindo classification. If grade III or above complications occur, they will be reported to the responsible unit of the project, fed back to the study supervision department, and comprehensively evaluated to how to deal with this situation in time and effectively. All follow-up will be performed by the project’s professional follow-up team. The trial will be completed until the last patient completes their follow-up.

**Table 1 T1:** Checklist for collection of necessary clinical data and follow-up schedule of enrolled patients.

	Baseline information				Follow-up (months)																
	Preoperation	Operation	POD 1-7	Discharge	1	3	6	9	12	15	18	21	24	27	30	33	36	42	48	54	60
Demography	√																				
Informed consent	√																				
Medical history	√																				
Oncological history	√																				
Tumor classification	√																				
Biometric data	√																				
Laboratory	√						√		√		√		√		√		√	√	√	√	√
Physical examination	√				√	√	√	√	√	√	√	√	√	√	√	√	√	√	√	√	√
Inclusion / Exclusion	√																				
Randomisation	√																				
Anamnesis	√				√	√	√	√	√	√	√	√	√	√	√	√	√	√	√	√	√
Gastroscopy	√								√				√				√		√		√
Enhanced thoracic and abdominal CT	√						√		√		√		√		√		√	√	√	√	√
Abdominal ultrasound	√						√		√		√		√		√		√	√	√	√	√
Concomitant Medication	√			√	√	√	√	√	√	√	√	√	√	√	√	√	√	√	√	√	√
Surgical information		√																			
Pathology				√																	
postoperative complications			√	√	√																
postoperative mortality			√	√	√																
local recurrence rate				√	√	√	√	√	√	√	√	√	√	√	√	√	√	√	√	√	√
surgical Apgar score		√																			
SF-36	√			√	√	√	√	√	√	√	√	√	√	√	√	√	√	√	√	√	√
EORTC QLQ-C30	√			√	√	√	√	√	√	√	√	√	√	√	√	√	√	√	√	√	√
EORTC QLQ-OES18	√			√	√	√	√	√	√	√	√	√	√	√	√	√	√	√	√	√	√
**Disease-free survival**					√	√	√	√	√	√	√	√	√	√	√	√	√	√	√	√	√
Overall survival					√	√	√	√	√	√	√	√	√	√	√	√	√	√	√	√	√

√, Indicates the need to collect the clinical data

SF-36, Short-Form 36; EORTC QLQ-C30, European Organization for Research and Treatment of Cancer Quality of Life Questionnaire Core 30; EORTC QLQ-OES18, Computerized adaptive test European Organization for Research and Treatment of Cancer Quality of Life Questionnaire for Esophageal cancer.

### Intervention

An equal number of patients will be randomly assigned to the RTA and TH groups. Details of the surgery are determined by the surgeons at each center as long as the tumor can be resected completely. If the tumor is difficult to be resect under minimally invasive conditions, the surgical strategy will be adjusted at that time.

The TH approach will be performed by distal esophagectomy and mediastinal lymph node dissection *via* the diaphragmatic hiatus under laparoscopy, whereas the RTA approach will be performed under thoracoscopy. The resection margin is a key indicator for evaluating the curative effect of surgery. The 5-year mortality of patients with positive resection margins is significantly higher than that of patients with negative resection margins (21).

According to the NCCN guidelines (6) and the Chinese expert consensus, for Siewert type II AEG with cT1 stage, the upper esophageal resection margin is recommended to be at least 2 cm away from the tumor, while for patients with cT2 stage or above, the upper esophageal resection margin is recommended to be at least 5 cm away from the tumor if the RTA approach is performed and at least 3 cm if the TH approach is performed. For patients in the former staging category, the lower resection margin is recommended to be at least 3 cm, while for patients in the latter staging category, a minimum of 5 cm is required to meet the surgical requirements. Laparoscopic proximal gastrectomy can be performed regardless of the surgical approach if the above criteria for the lower resection margin are met and at least more than half of the residual stomach remains.

In addition, total gastrectomy with D2 lymphadenectomy is recommended if the tumor involves more than 4 cm of the stomach. Lower mediastinal lymph node dissection is generally not required when the tumor is less than 2 cm away from the esophagus but is required when it is 2 cm or more. It is important to note that dissection of the upper, middle, and lower mediastinal lymph nodes is recommended once the tumor has invaded the esophagus at a distance of 4 cm or more. Postoperative reconstruction of the digestive tract will be determined by the surgeon’s personal experience and the patient’s situation. Proximal gastrectomy is feasible with gastric tube reconstruction and esophagogastrostomy. Roux-en-Y (esophagojejunostomy and jejunojeju-nostomy) reconstruction is recommended for total gastrectomy. In addition, minimally invasive surgery might need to be converted to open surgery if complications arise during the surgery. And participants may discontinue their participation at any time during the study.

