## Background

Adenocarcinoma of the esophagogastric junction (AEG) is defined as a tumor with an epicenter within 5 cm of the esophagogastric junction (EGJ) (1). Over the past two decades, the incidence of AEG has increased significantly, accounting for 5-8% of esophageal cancer in China and 35.7% of gastric cancer and lower esophageal cancer around the world (2–4). Siewert and Stein divided AEGs into three categories based on the distance between the tumor center and the EGJ. The epicenter of a tumor that measures between 1 and 5 cm above the EGJ is defined as type I, while that of an epicenter within 1 cm above and 2 cm below the EGJ is defined as type II, and those within 2–5 cm below the EGJ are defined as type III (5).

Currently, AEG is treated mainly by surgical resection. The National Comprehensive Cancer Network (NCCN) guidelines state that the management of Siewert type I should be similar to that of esophageal cancer, and the thoracoabdominal surgical approach (TA) is recommended because of its higher rate of thoracic lymph node involvement. Siewert type III should be managed as gastric cancer, and an abdominal-transhiatal surgical approach (TH) is recommended (6, 7). However, Siewert type II adenocarcinoma of the esophagogastric junction (Siewert II AEG) differs from the other two types in terms of its anatomical location and biological behavior, which is characterized by high differentiation, deep invasion, susceptibility to metastasis and adverse outcomes (8), making the proper operative approach for Siewert II AEG controversial.

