### The exclusion criteria are as follows

·Siewert type I and III adenocarcinoma of the esophagogastric junction confirmed histologically·A tumor that extends more than five centimeters from the EGJ or has developed distant metastases (M1) or peritoneal invasion·Significant cardiovascular disease, such as coronary atherosclerosis or myocardial infarction, with symptoms in the past 6 months·Significant respiratory disease, defined by whether the forced expiratory volume in 1 second (FEV1) is less than 1.5 L/s·History of right thoracotomy, adhesions to the right pleura or prior epigastric surgery·Indocyanine green test is not less than 15% for significant cirrhosis or chronic liver disease·Overt central nervous system disorders, mental disorders, and psychological disorders·Significant coagulopathy that has not been modified by current technology·Significant endocrine disorders, such as uncontrolled diabetes·A disease that is seriously out of control, such as a recurrent infection·Tumor-related diseases that require emergency surgery due to special conditions such as bleeding, perforation and obstruction

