## Discussion

The incidence of adenocarcinoma at the esophagogastric junction (AEG) has increased from 22.3% to 35.7% in the last few decades (4). AEG is highly likely to recur and metastasize, which results in a poor outcome (27). Surgical resection is considered to be the main curative treatment with a favorable prognosis. As the minimally invasive techniques of laparoscopy and thoracoscopy are in widespread use, the choice of surgical methods has become more diverse. Lymph nodes may be dissected by various surgical approaches, which will have a strong impact on the prognosis. However, intense debate has raged for decades regarding the proper operative approach for AEG, especially for Siewert II AEG (8).

The previous literature has shown that the main surgical methods for Siewert II AEG include TH and TA (7). A 10-year follow-up of the JCOG9502 study in Japan showed that LTA was not only ineffective in improving overall or disease-free survival but also increased postoperative morbidity. Therefore, in cases of esophageal invasion depths under 3 cm in AEG type II tumors, they recommended avoiding the LTA approach. However, that study had some limitations, such as a failure to show survival differences between the two procedures, not including minimally invasive procedures, and using only LTA instead of the Ivor-Lewis approach (28).

In recent years, a large number of studies have shown that the LTA approach is inferior to the RTA in terms of the number of lymph nodes dissected, long-term survival, recurrence and prognosis, causing the LTA approach to fall out of favor (6, 14, 15, 29). Compared with the LTA approach, Blank et al. found that the RTA (Ivor-Lewis operation) had a significantly longer survival time than the TH approach. Multivariate analysis showed that the surgical type was an independent prognostic factor. Nevertheless, that study was a single-center, nonrandomized, controlled study that did not use minimally invasive surgery (10). In contrast, a single-center retrospective study found that the TH is more effective in achieving an optimal extent of lymph node dissection, reducing complications, shortening hospital stays, and promoting recovery (11). Although RTA has great advantages in mediastinal lymph node dissection, ensuring a negative esophagectomy margin and completing gastrointestinal reconstruction, it also invades the chest and increases the incidence of chest-related complications (10, 12).

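### The lower mediastinal dissection threshold is written as distance from the oesophagus, where length of oesophageal invasion was almost certainly meant

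*Protocol article*

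**What the plan says.** Two consecutive sentences in the Intervention section of the protocol article set the extent of mediastinal dissection.

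- First sentence: "Lower mediastinal lymph node dissection is generally not required when the tumor is less than 2 cm away from the esophagus but is required" once that same distance reaches 2 cm.
- Second sentence, in which the length named is a lower limit: "dissection of the upper, middle, and lower mediastinal lymph nodes is recommended once the tumor has invaded the esophagus at a distance of 4 cm".

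Other places that bear on the reading:

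- Background, definition of the population: "an epicenter within 1 cm above and 2 cm below the EGJ is defined as type II".
- Exclusion criteria: "A tumor that extends more than five centimeters from the EGJ" is not eligible.
- Intervention, on margins: for cT1 tumours "the upper esophageal resection margin is recommended to be at least 2 cm away from the tumor".
- Intervention, on the transhiatal (TH) operation: "The TH approach will be performed by distal esophagectomy and mediastinal lymph node dissection" through the hiatus. No nodal field or threshold is attached.
- Intervention, on discretion: "Details of the surgery are determined by the surgeons at each center as long as the tumor can be resected completely".

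No other section restates or corrects the 2 cm rule.

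**The concern.** The two sentences look like steps of one scale but are written on different axes. The first measures separation from the oesophagus, the second extension into it. A tumour that invades the oesophagus is 0 cm away from it, so on the words used it falls in the lenient branch, while a tumour lying well clear of the oesophagus would need mediastinal dissection. That runs backwards.

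This is a rule that is stated and stated wrongly, so the allowance for detail that an article leaves to a fuller protocol does not cover it. Mediastinal dissection matters in this trial: the Discussion expects better mediastinal clearance with the right thoracoabdominal (RTA) approach, and the Objective lists the number and location of removed nodes as a secondary outcome. The Surgical quality control section calls for review when node dissection falls short of requirements, and in the article only these two sentences say when mediastinal dissection is needed. What is at stake is a correct common criterion across the six centres.

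**Working it through.** The plan gives no figure to reproduce here. The check is a reading of the two rules plus simple geometry. Positions are in cm relative to the EGJ, which is taken as the lower end of the oesophagus.

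**Inputs**

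- Epicentre position e, positive above the EGJ: from -2 to +1 (Background).
- Eligible extent: no more than 5 cm from the EGJ, read as 5 cm on each side (Exclusion criteria).
- Cut-offs of 2 cm and 4 cm (Intervention).

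**Step 1. Can the mandatory branch apply?** Let the tumour extend a > 0 cm above its epicentre. Its clearance from the oesophagus is max(0, -(e + a)). This is largest at e = -2, where it equals 2 - a (or 0 if a exceeds 2).

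| a (cm) | Largest possible clearance (cm) |
|---|---|
| 0.1 | 1.9 |
| 0.5 | 1.5 |
| 1.0 | 1.0 |
| 2.0 | 0 |

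The clearance is always under 2 cm, and no assumption about tumour symmetry is needed. The only exception is the exact 2 cm boundary, if distance were measured from the epicentre instead of the tumour edge. The mandatory branch is therefore essentially empty for Siewert II.

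**Step 2. What the rules say about lower dissection, by length of invasion**

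| Invasion of oesophagus | As written | Read as length of invasion |
|---|---|---|
| 0 to <2 cm | generally not required | generally not required |
| 2 to <4 cm | generally not required | required |
| 4 cm or more | recommended, by the second sentence | recommended, by the second sentence |

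The two readings differ only in the middle row.

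**Step 3. Can eligible tumours fall in the middle row?** As an illustration, assume a tumour of length L centred on its epicentre. Its upper edge is e + L/2 and its lower edge lies L/2 - e below the EGJ. Invasion of 2 cm needs L = 2(2 - e). The lower edge is then 2 - 2e below the EGJ, which stays within 5 cm when e is at least -1.5.

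| Epicentre e (cm) | Smallest L for 2 cm of invasion (cm) | Lower edge below EGJ (cm) | Eligible |
|---|---|---|---|
| +1 | 2 | 0 | yes |
| 0 | 4 | 2 | yes |
| -1 | 6 | 4 | yes |
| -1.5 | 7 | 5 | yes, at the limit |
| -2 | 8 | 6 | no |

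Eligible tumours with an epicentre from 1.5 cm below to 1 cm above the EGJ can reach the band. This shows what is possible, not how often it occurs.

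**Step 4. Which meaning was intended?** Three things point to length of invasion. The gap reading empties the rule (step 1). The adjacent sentence uses length of invasion, and with it the three steps fit together: under 2 cm, 2 cm or more, 4 cm or more. The Discussion also reports a type II cut-off on that axis, "in cases of esophageal invasion depths under 3 cm in AEG type II tumors", although that concerns avoiding the left thoracoabdominal approach and is only weak support.

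**The case against.** The strongest case against is that this is a slip of English that the context repairs. The next sentence speaks of invasion over a distance, so a surgeon would take the first sentence as the lower step of the same scale, and nobody would adopt a reading that makes the rule empty. The rule is softened by its own hedges and by the discretion given to surgeons, who must have done each procedure at least 20 times. The margin sentences use the same phrase for a true gap, but between margin and tumour, so they do not prove what was meant here. Most of this stands, and it is why the point is minor. It does not make the sentence right: the wording sets a mandatory threshold on the wrong measure, and nothing else in the article supplies the correct one.

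A reader might infer two stronger things.

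- **That the two sentences contradict each other at 2 to under 4 cm of invasion.** They do not. In that band only the first sentence speaks. The conflict is with the evidently intended rule. At 4 cm or more the second sentence reads naturally as an exception to a general rule.
- **That the error biases the comparison or affects DFS.** One rule is stated for both arms, and nothing in the document shows a differential effect or any consequence for a statistical figure.

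**Conclusion.** The concern holds as a misstated operative rule of minor severity. Followed literally, the mandatory branch applies to virtually no eligible patient, and tumours invading the oesophagus by 2 to under 4 cm come under the branch where lower dissection is generally not required. The emptiness of the mandatory branch rests only on the Siewert II definition and on taking the EGJ as the lower end of the oesophagus. The tumour lengths in step 3 also assume a tumour centred on its epicentre, which the document does not state.

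How many patients would fall in the band cannot be derived. The practical effect is probably small, and some variation in dissection would remain after the correction because details are left to the surgeons. The gain is a correct criterion across centres for quality monitoring and for the lymph node secondary outcome.

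**What to change.** Restate the first sentence as length of oesophageal invasion, so that the rules form one scale:

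- under 2 cm: lower mediastinal dissection generally not required;
- 2 cm or more: lower mediastinal dissection required;
- 4 cm or more: upper, middle and lower mediastinal dissection recommended.

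Say that the scale applies identically in both arms. The investigators should confirm the 2 cm and 4 cm cut-offs against their clinical source, which is not available here. The cost is a wording amendment to one sentence, with no extra patients, procedures or data.
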